## Methods

### Study design and participants

This protocol is a randomized, parallel-group, evaluator-blind, sham-controlled clinical trial, with an allocation ratio of 1:1, prospectively registered at ClinicalTrials.gov (NCT NCT05042115) on September 4, 2021, and follows SPIRIT 2013 and TIDiER-placebo recommendations [13, 14] for clinical trials.

Individuals diagnosed with nonspecific CLBP for at least 3 months will be included, with a mean numerical pain scale (NPE) score of at least 3 points and aged between 20 and 60 years [11]. Individuals undergoing concomitant physiotherapeutic treatment, individuals with medical contraindication to exercise, smokers/alcoholics, severe vertebral or neural pathologies, previous spine surgeries, cardiorespiratory disease, CLBP as a secondary complaint, pregnancy, hearing problems, or illiteracy and those who present an increase in symptoms in the stages of the study will be excluded.

On the day of the initial assessment (M0), all eligible participants will be informed about the procedures and objectives of the study and, after agreeing, they will sign an informed consent form (ICF), being able to voluntarily interrupt their participation in the study at any experiment stage. All study procedures were approved by the Research Ethics Committee at State University of the North of Paraná - UENP (CAEE: 43063621.3.0000.8123) and followed the Declaration of Helsinki.

The procedures will be carried out in reserved rooms of the same clinic in order to avoid any type of exposure or possible embarrassment to the participants. In the event of the possibility or presence of any type of real or potential embarrassment perceived by the participants or researchers, the intervention will be stopped immediately. All procedures will be conducted by the researcher ([name]) with experience of more than 7 years in the proposed procedures, and the evaluation will be conducted by one professional of clinical physiotherapy at the State University of the North of Paraná, previously trained in outcomes measurement. To characterize the participants, the following data will be collected: gender, age, duration of pain (months), weight, height, physical activeness, and use of medication.

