### Sample size

The sample size was calculated to detect an effect between groups for the pain intensity outcome assessed using the numerical scale. For the calculation, a power of 80% and an alpha error of 5% were adopted and, based on the results obtained by Rizzo et al. [11], a standard deviation of 2.0 points and an average difference of 1.3 points were considered, which resulted in a total sample size of 52 individuals. Considering possible sample losses, there will be an increase of 15% in the sample size calculated, totalizing 60 participants. All calculations were performed on the software G*Power version 3.1.9.7 [34].

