### Statistical analysis

To analyze the population profile data, we will use the descriptive statistical method and the results will be presented with mean values, medians, standard deviations, minimum and maximum values, and confidence intervals.

Data normality will be determined using the Shapiro-Wilk test, and the comparison of variables between groups at baseline will be performed using Student’s *t*-test for unpaired data for data with normal distribution or the Mann-Whitney test for non-normal data.

Comparisons of primary and secondary outcomes between groups and moments will be performed using the analysis of variance technique for repeated measures model in the two-factor scheme. Repeat measurement data will be checked for sphericity violation using Mauchly’s test, and the Greenhouse-Geisser correction will be used when sphericity is violated.

To analyze the moments, Bonferroni’s post-test for normal distribution or Dunnet’s post-test for non-normal distribution will be used, and the analysis of the different moments between the groups will be carried out using Student’s *t*-test for unpaired data with normal distribution or Mann-Whitney test for non-normal data.

The adopted statistical significance will be set at 5%. Analyses will be performed using the Statistical Package for the Social Sciences software—version 22.0 (SPSS Inc., Chicago, IL, USA) by a researcher blinded to treatments and group allocations using a coded spreadsheet. All the randomized participants will be included in the analysis, in accordance with intention-to-treat principles. To consider all participants, the missing data will be addressed according to the last observation carried forward (M0 or M1) [36]. Analysis and results from this study will be conducted by an independent biostatistician and checked for accuracy.

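### Adding the M0 score as a covariate to the between-group comparisons at M1 and M2 would gain precision at no extra data cost; the planned tests are valid but inefficient

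*Protocol article*

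**What the plan says.** All references are to the protocol article. Under Outcomes, every outcome is assessed at three moments: M0 (before treatment), M1 (straight after the last session) and M2 (four weeks later).

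Under Statistical analysis, two between-group analyses are fixed:

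- A two-factor model: "Comparisons of primary and secondary outcomes between groups and moments will be performed using the analysis of variance technique for repeated measures model". Since M0 is one of the moments, baseline becomes a level of the repeated factor.
- A comparison of the arms at each moment: "the analysis of the different moments between the groups will be carried out using" an unpaired Student t-test if the data are normal, otherwise a Mann-Whitney test. Normality is judged by Shapiro-Wilk.

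The section names no covariate, ANCOVA or change score. Apart from its place in the ANOVA, the M0 value serves only for a baseline test between the arms and as a value to carry forward when later data are missing.

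Under Sample size, the planning target is a difference between arms in pain intensity: "a standard deviation of 2.0 points and an average difference of 1.3 points were considered".

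**The concern.** The between-group pain difference at M1 or M2 would be read from the per-moment tests, and these use the raw follow-up score alone. Part of the spread in that score is stable variation between participants that M0 already measures. Leaving it in the error term widens the confidence interval. With about 30 per arm and simple randomisation, it also lets a chance baseline difference pass into the point estimate.

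The ANOVA does not clearly make up for this. Its group main effect pools M0 with M1 and M2 and so shrinks the difference it is meant to detect. Its interaction does use baseline, but it has two degrees of freedom and does not itself give an estimate in points with an interval. The section does not say which term carries the conclusion.

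A smaller matter is the effect measure. Sample size is planned on a mean difference, which a Mann-Whitney test does not estimate. If a normality test makes the choice, the reported contrast may not be the planned one.

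What is at stake is precision and interpretability in a trial of 60, not the validity of the tests.

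**Working it through.** **Inputs from the documents.** Difference 1.3 and SD 2.0 ("a standard deviation of 2.0 points and an average difference of 1.3 points were considered"); "a power of 80% and an alpha error of 5% were adopted"; "which resulted in a total sample size of 52 individuals"; 60 after the allowance for losses ("there will be an increase of 15% in the sample size calculated, totalizing 60 participants"); "with an allocation ratio of 1:1".

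**Assumptions.** Two-sided 5%. Correlation ρ between moments 0.3 to 0.7 (not in the documents). For the ANOVA terms, compound symmetry and true differences of 0, 1.3 and 1.3 at M0, M1 and M2.

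**1. The plan's own figure.** A two-sided two-sample comparison with these inputs needs 38 per arm (76) by the normal formula or 39 per arm (78) by the t distribution; one-sided, it needs 60. None gives 52. The figure 52 does appear for a repeated-measures ANOVA between-group test with f = 1.3/(2 × 2.0) = 0.325, three measurements and ρ = 0.5: λ = 52 × 0.325² × 3/(1 + 2 × 0.5) = 8.24, power 0.804. It also appears with two measurements and ρ = 0.3. The article states neither a correlation nor this test, so this is only a possible reconstruction. The next step reproduces: 52 × 1.15 = 59.8, rounded to 60.

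**2. Planned t-test at one moment.** SE = 2.0 × √(2/n), noncentrality = 1.3/SE.
- n = 30 per arm: SE 0.516, noncentrality 2.52, 58 df, power 70%.
- n = 26 per arm: SE 0.555, noncentrality 2.34, 50 df, power 63%.

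**3. ANCOVA at one moment.** Residual SD = 2.0 × √(1 − ρ²), one df fewer.

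| ρ | Variance removed (ρ²) | Residual SD | Power, N = 60 | Power, N = 52 |
|---|---|---|---|---|
| planned t-test | – | 2.00 | 70% | 63% |
| 0.3 | 9% | 1.91 | 74% | 67% |
| 0.5 | 25% | 1.73 | 82% | 76% |
| 0.7 | 49% | 1.43 | 93% | 90% |

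If ρ were 0, the lost degree of freedom would cost under one point of power.

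**4. ANOVA group main effect.** Mean difference over the three moments = (0 + 1.3 + 1.3)/3 = 0.87. SD of a participant's mean = 2.0 × √((1 + 2ρ)/3). At ρ = 0.5 this is 1.63, and power at N = 60 is 52%.

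**5. ANOVA group-by-moment interaction.** λ = (n/2) × Σ(δ − mean δ)²/(SD² × (1 − ρ)), with Σ = 0.87² + 2 × 0.43² ≈ 1.127. At n = 30 and ρ = 0.5, λ = 15 × 1.127/(4 × 0.5) = 8.45 on 2 and 116 df, power 73%.

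| N = 60 | ρ = 0.3 | ρ = 0.5 | ρ = 0.7 |
|---|---|---|---|
| Interaction (2 df) | 58% | 73% | 92% |
| ANCOVA, one moment | 74% | 82% | 93% |

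ANCOVA beats the t-test throughout the range. Its margin over the interaction is wide at ρ = 0.3 and nearly gone at 0.7.

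**The case against.** Four objections deserve an answer.

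- **The planned tests are valid.** Under randomisation an unadjusted comparison is unbiased with correct type I error, and its standard error already allows for chance imbalance. This stands. A reader might infer that the results would be biased by baseline differences; nothing in the documents supports that. The loss is of efficiency.
- **The ANOVA does use baseline.** A reader might infer that the whole plan ignores baseline, or that 52% is the power of the ANOVA. Neither holds. The interaction is the usual treatment test in such a design and uses M0 much as a change score does; 52% belongs to the main effect alone, and the article does not say that the conclusion rests on it.
- **The size of the gain is unknown.** A reader might infer that adjustment recovers most of the power lacking at 60. That needs ρ of about 0.5 or more and all 60 analysed. At 0.3 the gain is only 4 points, from 70% to 74%. The entry criterion of at least 3 points on the pain scale truncates the baseline range, which tends to lower ρ. The extra participants are meant to cover losses, and the effect of carrying values forward is not in these figures.
- **The normality gate costs little power.** In a simulation of rounded 0–10 scores (30 per arm, SD 2, difference 1.3), which I have not repeated, the gated procedure had 67–68% power against 68–69% for the t-test. What remains is the choice of effect measure, not power.

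**Conclusion.** The point holds as a free improvement. The arms are compared at M1 and M2 on raw scores, M0 enters the ANOVA as an outcome moment, and the one term that uses baseline gives no single effect estimate. For pain intensity with 60 analysed, adjustment at one moment raises power from 70% to about 74%, 82% or 93% at ρ = 0.3, 0.5 or 0.7; with 52 analysed, from 63% to 67%, 76% or 90%.

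These figures rest on the protocol's 1.3 and 2.0, a two-sided 5% level and an assumed ρ. They apply to the pain scale only; the article gives no planning values for Oswestry or pressure threshold, although the direction of the gain is the same. That 52 does not follow from the stated inputs is a separate matter. It makes spare precision more valuable here but adds nothing to this point's weight.

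Because the article states its methods outright, this is not a detail left to an unseen analysis plan.

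**What to change.** In the Statistical analysis section:

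- Make the main between-group analysis of the pain scale, Oswestry and pressure threshold a repeated-measures model of M1 and M2, with group, moment, their interaction and the M0 value as covariate.
- Report the adjusted mean difference with its 95% CI at each of M1 and M2. This requires no single primary moment, which the article does not name.
- Keep the Mann-Whitney test as a sensitivity analysis, and do not let a normality test choose the reported effect measure.
- Do not apply the adjustment to the improvement scale, which itself rates change.

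The cost is a wording change and one degree of freedom for the covariate. M0 is already collected, so no visits, measurements or participants are added. The change should be recorded through the route in the Protocol amendments section, before the analyst sees outcome data by arm.

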### Outcomes

Participants will be evaluated by a researcher blind to allocation and the evaluative moments for all outcomes will correspond to the pre-intervention (M0), immediately after the last meeting (M1) and reassessed again in the follow-up of four (M2) weeks after the end of the protocols (Fig. 2).

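### Carrying the last observation forward, including the baseline score, can bias the treatment difference in either direction, and costs power when losses come before M1

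*Protocol article*

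**What the plan says.** The Statistical analysis section of the protocol article includes all randomised participants under intention-to-treat and gives one rule for missing outcomes: "the missing data will be addressed according to the last observation carried forward (M0 or M1"). M0 is the pre-intervention assessment. The Outcomes section places the other two "immediately after the last meeting (M1) and reassessed again in the follow-up of four (M2) weeks after the end of the protocols". The main comparison is the "analysis of variance technique for repeated measures model in the two-factor scheme", followed by unpaired t-tests or Mann-Whitney tests between groups at each moment.

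On losses, the Sample size section says only that "there will be an increase of 15% in the sample size calculated, totalizing 60 participants". No section says when losses are expected or whether they will be balanced between arms. The Study design and participants section also excludes people whose symptoms increase during the study, and does not say whether they are still assessed.

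**The concern.** Carrying M0 forward assumes that someone who leaves before M1 would have stayed at the pre-treatment score. That is implausible here. Both arms receive four sessions of education and hypnosis, which the Background describes as effective, so both should improve. An early dropout then contributes zero improvement, entered as if it had been observed.

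Two consequences follow. If the arms lose people equally, the difference is pulled towards zero. If they lose people unequally, the arm with more dropouts looks worse whatever the treatments do. Including every randomised participant does not remove either bias.

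The plan is also inconsistent with itself. The sample size allows for losses as if they leave and 52 informative participants remain, whereas the analysis keeps them with carried-forward scores. The exclusion for increased symptoms adds an outcome-related route: if such a person is not assessed again, an earlier and better score replaces a worsening.

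**Working it through.** **Inputs from the protocol article.** "a power of 80% and an alpha error of 5% were adopted"; "a standard deviation of 2.0 points and an average difference of 1.3 points were considered"; "which resulted in a total sample size of 52 individuals"; 60 enrolled "with an allocation ratio of 1:1", so 30 per arm. Going from 60 to 52 is 8 losses, or 8/60 = 13.3%; the stated allowance is 15%.

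**Assumptions not in the article.** Two-sided 5%; correlation r = 0.5 between moments; improvement c of 2 to 2.5 points in the control arm; dropout unrelated to outcome; an effect stable from M1 to M2; timing and balance of losses as shown.

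**1. The plan's own figure.** A two-sided, two-sample t-test with SD 2.0 and difference 1.3 needs 78 in total, not 52. A repeated-measures ANOVA, between-groups factor, reproduces it: f = (1.3/2.0)/2 = 0.325, three measurements, r = 0.5.

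λ = N·f²·m/(1+(m−1)r) = 52 × 0.1056 × 3/2 = 8.24, giving power 0.804.

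Then 52 × 1.15 = 59.8, so 60. The correlation is inferred; two measurements with r = 0.3 also give 52.

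**2. Bias when all losses precede M1.** With loss qT (osteopathic arm) and qC (control), the expected difference in improvement is (1−qT)(c+δ) − (1−qC)c.

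- Equal loss, 15%, δ = 1.3: 0.85 × 1.3 = 1.105. At 13.3% it is 1.127. Type I error stays at about 5%.
- No effect, control loses 20% and osteopathic arm 6.7% (6 and 2 of 30): 0.133 × 2 = 0.27, or 0.133 × 2.5 = 0.33. Simulated type I error was about 7.5 to 9% with random numbers of dropouts, and 6.8% with exactly 6 and 2.
- δ = 1.3, osteopathic arm loses 20% and control 6.7%: 0.8 × 3.3 − 0.933 × 2 = 0.77 for c = 2; 0.8 × 3.8 − 0.933 × 2.5 = 0.71 for c = 2.5.
- δ = 1.3, control loses more, c = 2: 0.933 × 3.3 − 0.8 × 2 = 1.48.

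**3. Power of the t-test at M2.** 30 per arm, 15% loss in each arm, c = 2.5. Mixing carried-forward baselines with treated scores also widens the SD: the arm variance is 4 + q(1−q)(improvement)², where q is the fraction lost early. At q = 0.15 the average variance is (5.84 + 4.80)/2 = 5.32, so the SD is 2.31.

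| Timing of losses | Mean estimate | Power, carried forward | Power, observed M2 only |
|---|---|---|---|
| No loss | 1.30 | 70% | 70% |
| All before M1 | 1.1 | about 45% | about 62–63% |
| Half before M1 | 1.2 | about 55% | about 62–63% |
| All after M1 | 1.3 | about 69% | about 62–63% |

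Simulation agreed with the closed form. With baseline adjustment and all losses early, power is about 56% carried forward against about 74% on observed data.

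**4. Power on the calculation behind N = 52.** At N = 60 with the difference scaled by (1−q): 13.3% loss gives λ = 7.14 and power 0.75; 15% gives λ = 6.87 and power 0.73. The plan is 0.80, so the worst timing costs about 5 to 7 percentage points. This ignores the wider SD.

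**The case against.** A reader might infer that this rule takes power well below the planned 80% at the dropout the protocol expects. The document does not support that.

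- The 15% is an allowance for possible losses, with no timing or balance stated. There is a further assessment four weeks after M1, and missed sessions are to be rebooked. If all losses follow M1 and the effect is stable, carrying M1 forward causes no bias and does better than dropping the missing M2 values (69% against about 62–63%).
- The t-test has only 70% power at N = 60 with no loss, and 63% with 52 completers. That part of the gap to 80% comes from the sample-size basis.
- Setting an unadjusted carried-forward t-test (about 45%) against a baseline-adjusted analysis of observed data (about 74%) would change two things at once. Like for like, the gap is about 45% to 63% unadjusted and 56% to 74% adjusted.
- The unequal-loss scenario is assumed. With 1 point of improvement the false difference is 0.133 × 1 = 0.13 and type I error about 5.6%; the reverse imbalance works against the osteopathic arm.
- The simulated dropout is unrelated to outcome, the setting kindest to a mixed model.

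All of this stands, and limits the size. It does not remove the bias: carrying M0 forward is a stated rule rather than a detail left open, and it distorts the difference whenever losses precede M1 and participants improve.

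**Conclusion.** The concern holds as one of bias whose direction cannot be known in advance, with a power cost confined to losses before M1. At 15% equal early loss the difference falls from 1.3 to about 1.1 points. With 20% against 6.7% early loss and 2 to 2.5 points of improvement, the false difference is about 0.27 to 0.34 with type I error of about 7 to 9%, or a true 1.3 is estimated as about 0.7 to 0.8 if the osteopathic arm loses more. The power cost ranges from nothing (all losses after M1) to about 5 to 7 points on the model that reproduces N = 52. For the M2 t-test with all losses early it is about 18 points against observed data. SD, difference and numbers per arm come from the protocol; correlation, improvement, timing and balance of losses are assumed. Confidence is high on the existence of the bias and moderate on its size. The change should be made before any unblinded analysis.

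**What to change.** Replace last observation carried forward as the main rule with one of:

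- a likelihood-based linear mixed model on all observed M1 and M2 values, with group, moment, group-by-moment and baseline score (MIXED in the SPSS already named); or
- multiple imputation by arm.

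Keep all randomised participants in the analysis set. State how those with only M0 are handled: with baseline as a covariate they supply no outcome value to the mixed model, whereas imputation gives them one.

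Add one sensitivity analysis for outcome-related missingness, for example making missing osteopathic-arm values worse by a stated amount, because participants whose symptoms increase are excluded during the study. Carried-forward results may be kept as a secondary analysis.

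The cost is revised wording and slightly more programming, with no extra participants, visits or software. The main analysis would rest on a missing-at-random assumption, and would give up some power relative to carrying forward if all losses fall after M1 and the effect is stable.

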### Auditing

The Research Ethics Committee of the State University of the North of Paraná (UENP) will check during the project the presence and the completeness of the investigation files, such as inclusion and exclusion criteria, informed consents, data collections, and storage.

### Protocol amendments

All substantial amendments will be notified to the ethics committee of the State University of the North of Paraná (UENP). If amendments concern or affect participants, they will be informed about the changes, and if needed, additional consent will be requested and registered. Also, online trial registries will be updated accordingly.

### Confidentiality

All data extracted from the participants are strictly confidential, being related to the participants through codes, to which only the researchers will have access, guaranteeing their confidentiality. The data extracted from the participants regarding the characterization and outcomes of this study will be recorded in individual forms and later stored in digital spreadsheets (Microsoft Office), ensuring the same secrecy and confidentiality mentioned above.

### Data access

The access to the final trial dataset will be available in a repository from the State University of the North of Paraná (UENP).

### Ancillary and post-trial care

The clinic of the State University of the North of Paraná will be available to all participants of this study for follow-ups of their clinical status. In addition, all participants who wish to continue treatment, sham therapy or OMT, will be placed on the clinic’s registration list.

### Dissemination plan

The researchers consider data sharing to be an important component of clinical research. All the data will be published in international peer-reviewed journals. In addition, the results of this study will be communicated to the participants, healthcare professionals, and on social media. We also plan to present our data at relevant international congresses and conferences across South America and, if possible, in other continents.

